## Biological samples

No biological sample will be stored during the trial.

# ELIGIBILITY CRITERIA

## Inclusion criteria

- Age ≥ 75 years
- Admission to the emergency departmentwith a diagnosis of AHF determined by the emergency physician, based on the presence of:
  - at least one of the following symptoms: acute, or worsening of dyspnea, orthopnea
  - one or more of the following: pulmonary rales, peripheral edema, a chest radiograph or transthoracic ultrasound showing pulmonary vascular congestion signs, increased natriuretic peptides (BNP or NT pro BNP).
  - Patients affiliated to French social security (“AME excepted”))
  - Written informed consent signed by the patient / the trustworthy person / family member / close relative, or inclusion in case of emergency and written informed consent will been signed by the patient (if need be by trustworthy person, family member or close relative) as soon as possible (article L1122-1-2 of the French Public Health Code)

## Exclusion criteria

Patients are excluded if they have any of the followings:

- Other obvious cause of acute illness (severe sepsis, ST elevation Myocardial infarction)
- Systolic blood pressure less than 100mmHg
- Any contra-indication to nitrates (severe mitral or aortic stenosis, or severe aortic regurgitation)
- Known chronic kidney injury on dialysis
- Time from ED entrance to inclusion > 6h,
- Patient under legal protection measure (tutorship or curatorship) and patient deprived of freedom

## Enrolment procedure

The 15 recruiting centers are:

| **City** | **Country** | **Hospital** | **Unit** |
| --- | --- | --- | --- |
| Paris | France | Pitié-Salpêtrière | Service des Urgences |
| Bobigny | France | Avicenne | Samu 93 |
| Paris | France | Saint-Antoine | Service d’Accueil des Urgences |
| Paris | France | HEGP | Service d’Accueil des Urgences |
| Tours | France | CHU Tours | Département de Médecine d’Urgences |
| Nîmes | France | CHU Nîmes | Pôle Anesthésie Réanimation Douleurs Urgences |
| Nancy | France | CHU Nancy | Service des Urgences / SAMU / SMUR |
| Toulouse | France | CHU Rangueuil | Service des Urgences |
| Paris | France | Lariboisiere | Service des Urgences / SMUR |
| Paris | France | Cochin | Service des Urgences |
| Nice | France | CHU Nice | Service des Urgences |
| Creteil | France | CHU Henri Mondor | Service des Urgences |
| Boulogne | France | CHU Ambroise Paré | Service d’Accueil des Urgences |
| Paris | France | CH Saint-Joseph | Service des Urgences et Lits d’Urgence |
| Besançon | France | CHU Besancon | Service d’Accueil des Urgences |

In the case where one center withdraw from the trial before its start, we will invite another ED to participate (two centers are listed as willing to participate if possible – CHU Nantes and CHU Lyon).

Patients will be included by the emergency physicians whilst working in the ED. After a patient is suspected of AHF, the physician in charge (with the help of clinical research technician if present) will sought any exclusion criteria before seeking patient’s informed consent. To improve adherence to the bundle, after each center switches to the intervention period, a clinical research technician will be working in the ED during training period).

The present research team and its study coordinator ([name]) has conducted several previous studies in these 15 centers (among others) where patients were included and followed as planned: 1000 patients (30 centres) in 1 month [NCT02738164, [name] et al. JAMA 2017]; 500 patients (4 centers) in 1 year [NCT01774500 PlosOne 2014]; 1800 patients (14 centres) in 1 year (NCT02375919, *JAMA 2018*); 550 patients (13 centers) in 3 months (NCT02926664,*, EJEM 2018)*). Each of these prospective multicenter studies coordinated by [name], the scientific director of the present ELISABETH trial achieved full targeted recruitment within the pre specified timeframe.

**Thus, the target of 4 patients per month per site seems highly achievable.**

*In the case where one center withdraw from the trial before its start, we will invite another ED to participate (two centers are listed as willing to participate if possible – CHU Nantesand CHU Lyon). In the case where one center should withdraw from the study after the beginning of the trial, the steering committee will evaluate mid-term recruitment after 16 weeks and adjust the remaining period to ensure that all groups will have the same total period length of inclusion, and similar sample size.*

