| Center 11 | C | C | C | C | C | C | C | … | I | I | I | I | I |
| Center 12 | C | C | C | C | C | C | C | … | I+T | I | I | I | I |
| Center 13 | C | C | C | C | C | C | C | … | C | I+T | I | I | I |
| Center 14 | C | C | C | C | C | C | C | … | C | C | I+T | I | I |
| Center 15 | C | C | C | C | C | C | C | … | C | C | C | I+T | I |

*Figure 1: stepped wedge organisation and timetable of the trial*

C: Control period. I: Intervention period. T: training

**In the case where one or more centers will have to drop out of the trial, a mid-term reevaluation of the period distribution will be conducted by the steering committee in order to ensure similar repartitions of period and number of patients in each group.**

This trial is comparative: intervention period vs control period. In the intervention period, patients will be treated according to the care bundle. In the control period, patients will be treated as usual (TAU) by the emergency physicians, without the aid of a care bundle.

Due to the design of the study (stepped wedge) and the intervention, there will be no blinding of the physician and the patient.

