### Randomization

This is a stepped wedge randomisation. All centers will be randomised for their time of intervention implementation. Randomisation will be computer generated by a biostatistician from URC-Est, independent of the study and before the study beginning.

This is an open trial.

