# Specific committee for the study

## Steering Committee

**Members of the committee**: [name] (Primary investigator, anaesthesiologist), [name] (scientific coordinator, emergency physician), [name] (emergency physician), [name] (Cardiologist), [name] (geriatrician), [name] (clinical pharmacologist; and Methodologist), [name] (statistician), a representant of the promotor (DRCI head office project advisor)

**Missions:**Define the overall structure of the study, coordinate information, review the initial methodology and oversee the trial.

The committee can be asked to adjudicate any death in the study and relate whether it is from cardiovascular cause.

Rhythm of the meeting: 1meeting per years.

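### If a centre withdraws, the protocol lets the steering committee replace randomised switch times with chosen ones, to gain a balance that the analysis does not need

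*Protocol*

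**What the plan says.** Section 5.3 (Randomization) defines what is randomised: "All centers will be randomised for their time of intervention implementation". The list is produced by a biostatistician who is "independent of the study and before the study beginning". The same section adds: "This is an open trial".

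Section 5.1 (Design of the study) provides that, if one or more centres drop out, "a mid-term reevaluation of the period distribution will be conducted by the steering committee", with the aim of similar periods and patient numbers in each group. Section 7.3 (Enrolment procedure) gives the timing and the target. If a centre withdraws after the start, the committee assesses recruitment after 16 weeks and is to "adjust the remaining period to ensure that all groups will have the same total period length of inclusion, and similar sample size". A withdrawal before the start is handled separately, by inviting one of two reserve centres.

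Section 11.1 (Steering Committee) lists the primary investigator, the scientific coordinator and a statistician among the members. No section gives an algorithm, an order constraint or an independent party for the adjustment. Section 13.1 plans no interim analysis. Section 13.2 analyses the primary endpoint with a linear mixed model that has a random cluster effect and fixed effects for strategy and step.

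**The concern.** In a stepped-wedge trial the time of switching is the treatment allocation. Here an independent person generates it before the start, and a committee close to the trial may then change part of it mid-course. The trigger is a centre withdrawal and the information used is recruitment. Section 7.4 has recruitment followed at least every two weeks, and the preliminary study in section 7.3 found 6 to 13 patients per week per centre.

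If switch times are moved in the light of such figures, exposure can become linked to how a centre is doing at that time. The step effects remove calendar trends common to all centres, and the cluster effect addresses stable differences between centres. Neither restores random assignment of which centre switches when. A discretionary change made during the trial cannot be undone in the analysis. The question is whether the balance gained is worth this.

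**Working it through.** **Inputs.** Section 5.1 and Figure 1: 15 centres, 18 fortnights, a 4-week common control period, then one switch per fortnight. Section 13.4: SD 9, difference 3 days, 80% power, alpha 5% (taken as two-sided), ICC 0.0001, design effect 1.609, 454 analysed, 500 included.

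**1. The plan's own figures.**
- Individually randomised total: 4 × (1.960 + 0.842)² × 9²/3² = 282.6, so 283, as stated.
- Stepped-wedge design effect with k = 15 steps, one measurement per step, one baseline measurement and n = 2 per cell: [1 + ρ(kn + n − 1)] / [1 + ρ(kn/2 + n − 1)] × 3(1 − ρ) / [2(k − 1/k)] = (1.0031/1.0016) × (2.9997/29.867) = 0.1006. Times 16 measurements this is 1.609, as stated.
- 282 × 1.609 = 453.7, against the stated 454. 454 × 1.10 = 499.4, so 500.

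**2. Planned balance.** The centre in slot k has k + 1 control fortnights and 17 − k intervention fortnights. Summed over 15 slots this gives 135 control and 135 intervention centre-periods.

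**3. Switch times still open.** Slot k switches at week 5 + 2(k − 1), so slots 1 to 6 have switched by week 15. After week 16, slots 7 to 15 remain: nine times, or eight if the lost centre is itself one of them.

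**4. Balance if one centre is lost after week 16 and nothing is moved.** Ten centre-periods disappear. For slot k, max(0, k − 7) of them are control.

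| Lost slot | Control v intervention | Control share p | 1 − 4p(1 − p) |
|---|---|---|---|
| 1 to 7 | 135 v 125 | 51.9% | 0.15% |
| 12 | 130 v 130 | 50.0% | 0% |
| 15 | 127 v 133 | 48.8% | 0.05% |

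Over all slots and withdrawal times the extremes are 120 v 133 (47.4%) and 135 v 119 (53.1%). The efficiency costs there are 0.26% and 0.40%. The index 4p(1 − p) is a two-group measure and ignores the period structure, so step 5 uses the model itself.

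**5. Power under the section 13.2 model.** Generalised least squares on cell means, with fixed period effects and a random cluster effect, and 454/270 = 1.68 patients per cell. Power = Φ(3/SE − 1.96).

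| Schedule | SE | Power |
|---|---|---|
| All centres kept | 1.137 | 75.2% |
| Slot 8 lost after week 16 (134 v 126) | 1.151 | 74.1% |
| Slot 12 lost (130 v 130) | 1.169 | 72.8% |
| Slot 15 lost (127 v 133) | 1.210 | 69.8% |

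The other slots lie between 69.8% and 74.1%. The starting value is 75.2% rather than 80% because 1.609 corresponds to 16 measurements while the schedule has 18 fortnights. That is a separate matter.

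**6. Source of the loss.** Losing slot 12 leaves the groups exactly equal, yet power still drops by 2.4 points. Losing slot 8 leaves them unequal, yet power drops by only 1.1 points. The loss comes from the missing data and where they sat in the schedule, not from unequal totals.

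**The case against.** Several points limit the concern, and most of them stand.

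- A reader might infer that the randomised order is overridden. The clauses speak of the remaining period and the distribution of periods; neither mentions re-ordering. An equal shift of all remaining switches would satisfy them and keep the order. What the text does allow is a change of times, and time is what section 5.3 randomises.
- A reader might infer that centres are picked by their recruitment, or that the committee acts on outcomes. The stated aim is at group level, the review is of recruitment, and no interim analysis is planned. Open treatment does not mean that outcomes are seen by period. The text simply does not rule out centre-by-centre changes.
- It would be too strong to say that inference is invalidated. The primary analysis is a mixed model with step effects, and this document plans no permutation test on the order. A common shift is largely absorbed by the step effects.
- The yearly meeting ("Rhythm of the meeting: 1meeting per years") does not contradict a review at week 16. It is the routine rhythm; the review is a separate, triggered task.
- The clause acts only if a centre withdraws after the start.

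The best argument for flexibility is that re-timing can recover power. Suppose slot 15 is lost and the eight remaining switches are each delayed by one fortnight. The split becomes 127 + 8 = 135 v 133 − 8 = 125, and the same model gives 74.1% instead of 69.8%. But the totals then differ by 10 instead of 6. The gain comes from more fortnights with both conditions running, not from equality, which is the clause's stated target. It also comes from a common shift, which needs no discretion over individual centres.

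**Conclusion.** The concern holds in a limited form. After a withdrawal, a non-independent committee in an open trial may replace up to nine remaining randomised switch times with chosen ones, using recruitment data and no pre-specified rule. The purpose, equal period length and sample size, is not needed. For a loss after week 16 the imbalance costs at most 0.15% of efficiency (at most about 0.4% for a loss at any time), and the planned mixed model accepts unequal cells. The power loss of 1.1 to 5.4 points belongs to the lost centre's data.

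These figures assume one centre lost, 454 patients spread evenly over 270 cells, SD 9 and ICC 0.0001. The size of any bias from chosen times cannot be computed from the document, and nine is a ceiling, not an expectation. This is a cheap improvement that should be made, not a defect that endangers the trial if no centre withdraws.

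**What to change.** In sections 5.1 and 7.3, delete the equalising adjustment. State that the pre-generated switch times of the remaining centres stand, that a lost centre's later cells stay empty, and that its patients to date are analysed as randomised.

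If the sponsor wants flexibility, replace the committee's discretion with a rule fixed before enrolment and applied by the independent biostatistician, which shifts all remaining switches equally and preserves their order.

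The cost is protocol wording. Under the first option, group sizes may be slightly unequal after a dropout, and the power that a common delay might recover after the loss of a late-switching centre is given up. The second option keeps that possibility, but the rule has to be written in advance.

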## Inclusion rate

We aim to have balanced population between the two groups, especially in terms of number of patients analysed in each group. Furthermore, to avoid any period effect, centers must include their targeted number of patients throughout the whole inclusion period. Therefore, we will closely monitor the number of patient recruited in each center. The local investigator or the CRT will follow at least once every 2 weeks how many patients were included and could be analysed.

# Termination and exit rules

## Criteria and procedure for premature withdrawals and exits from the study

- Subjects may exit the study at any time and for any reason.
- The investigator can temporarily or permanently withdraw a subject from the study for any safety reason or if it is in the subject's best interests.

🡺Subject lost to follow-up: the subject cannot be located. The investigator must make every effort to reconnect with the subject (and record his attempts in the source file), at least to determine whether the subject is alive or dead.

If a subject exits the trial prematurely or withdraws consent, any data collected prior to the date of premature exit may still be used.

The case report form must list the various reasons why the subject exited or was withdrawn from the study:

- Subject's personal reasons
- Explicit withdrawal of consent
- Lost to follow-up

### Procedure for replacing participants

If a subject exits the trial,this will in no way affect the standard care received for his/her condition.

### Full or partial cancellation of the study

AP-HP, as the sponsor, reserves the right to permanently suspend enrolment at any time if the enrolment targets have not been met.

# EFFICACY ASSESSMENt

## Description of parameters for assessing efficacy endpoints

The primary endpoint (days alive and out of hospital at day 30) will be measured at the end of the 30 days follow up period, either by hospital visit, phone interview, and medical chart review. Vital status, date of death and date of discharge will be collected.

A death during the follow up period will correspond to 0. An ED visit will correspond to “one day” at the hospital.

For example, a patient not admitted (at day 0), with no return visit to the hospital, and alive at day 30 will have 30 days alive and out of hospital.

A patient who is admitted (at day 0) and stays 8 days in the hospital before being discharged and have no readmission and no return visit to the ED would have a “22 days alive and out of hospital at 30 days”.

A patient that is admitted and die at 13 days, either at home or in hospital will have 0.

A patient that is admitted for 10 days, discharged home for 5 days then admitted at day 16 for 15 days will have 5 days alive and out of hospital (namely day 11, 12, 13, 14 and 15).

## Anticipated methods and timetable for measuring, collecting and analyzing the efficacy data

- In-hospital mortality will be obtained from hospital data base (Mediweb, Gilda, or Orbis) and phone interview with the last known ward of hospitalization of the patient. In case of transfer to another hospital, this data will be collected either by phone interview or hospital visit if necessary.
- 30 day all-causes mortality rate: same as above for patient still in hospital at day 30, phone call to the patients, relatives, or GP if not.
- Cardiovascular related 30 day mortality. Adjudicated by an adjudication committee (see below) as to whether the death has been mainly caused by a cardiovascular issue.
- Length of stay in hospital and changes of more than 2 fold in creatinine level from hospital database (CleanWeb, MediWeb, Gilda or Orbis)
- Efficacy data will be analyzed at the end of the study after data review and freezing of data base.

# SAFETY

During this research, adverse events (serious and non-serious) do not need to be reported to the sponsor. The report must instead be made as part of the vigilance procedure applicable to the product or intervention under investigation (pharmacovigilance

for a drug product; medical device vigilance for a medical device, etc.).

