| Other interventions added by the study | The intervention will not test any particular drug or medical disposal, but rather the application of the international guidelines (ESC, EUSEM, AHA) through the implementation of a protocol of care. The care bundle of early care with a checklist that includes the following checklist:   - Detection and treatment of AHF precipitating factors (infection, acute coronary syndrome or atrial fibrillation) - Treatment of congestion, including a protocol of nitrates titration, and low dose furosemide, as recommended by international guidelines - Non-invasive ventilation if indicated, as recommended by international guidelines - Preventive low molecular weight heparin, as recommended by international guidelines   During the control period, the standard of care will be treatment as usual, left at the discretion of the treating emergency physician |
| Expected benefits for the participants and for society | We anticipate a reduction in length of hospitalisation and rate of readmission. The intervention is aimed at increasing the number of days alive and at home in the first month after inclusion. This benefit for the patient should be associated with a reduction in the allocation of hospital resource. |
| Minimal risks and constraints added by the study | Minimal risk, as only recommended treatments will be administered  The intervention will not test any particular drug or medical disposal, but rather the application of the international guidelines (ESC, EUSEM, AHA) through the implementation of a protocol of care.  Validated treatment will be randomly attributed to a group of patients (List of interventions listed in the article L1122-1-2 of the French Public Health Code, and corresponding to a Minimal risks and constraints) |
| Scope of the study | Emergency care and acute heart failure |
| Number of participants included | 500patients |
| Number of sites | 15 centers in France  If one center withdraw from the trial before its start, we will invite another ED to participate (2 centers are listed as willing to participate if possible) |
| Schedule for the study | - inclusion period: 36 weeks - participation period (treatment + follow-up): 30 days - total duration: 36 weeks and 30 days |
| Number of enrolments expected per site and per month | 4 |

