**Control period: Acute heart failure standard therapy:**

- Treatments are given at the discretion of the treating emergency physician

The guidelines and standard of care will be recalled to the emergency physicians at the begining of the trial in each center when the control period will start.

**Intervention period: Early intensive care bundle:** The care bundle comprises a list of items to follow and tick on a handover checklist (see below-Figure 2) within 4 hours of ED management:

- a) Treatment of the congestion: *(international guidelines and recommendations* ^10,11^)
  - 40mg of Intravenous (iv) furosemide (or usual daily dose) if not already given pre-hospital.
  - IV nitrates given in boluses of 3mg every 5 minutes. After one hour of bolus titration, then continuous infusion with an hourly dose of at least half of total given during the first hour of nitrate. Blood Pressure (BP) will be monitored every 5 minutes during the titration (then hourly), and nitrates will be discontinued if BP drops <100mmHg.
- b) Treatment of precipitating factors :
  - Administration of antibiotic therapy (accordingly to local guidelines amoxicillin and clavulanic acid in most cases) if at least two of the following: Fever > 38°C, leucocytes > 12 000 G/L, radiological signs suggestive of lower respiratory tract infection or elevated CRP or PCT,
  - Administration of dual antiplatelet therapy and transfer to cardiac intensive care unit if at least 2 of the followings: chest pain, ischemic signs on ECG, elevated troponin concentration or change in troponin concentration. These patients will be transferred for coronary angiography if indicated by the cardiologist, as recommended.^40^
  - In case of atrial fibrillation: administration of heparin, heart rate control strategy (digoxin or amiodarone as indicated) to reduce heart rate under 100 bpm, early admission to a cardiac intensive care unit if elevated troponin associated.
- c) NIV if respiratory distress with hypercapnia and pH < 7.35 in absence of contra indication.^11^
- d) Preventive LMWH if no pre-existing anticoagulation therapy.^11^

**All treatment will be initiated in the ED, and their continuation or discontinuation will be evaluated by the treating physician during the subsequent hospital stay.**

**
[figure not shown]
**

*Figure 2: example of handover sheets with checklist for AHF management*

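### The bundle checklist prompts three antithrombotic treatments in patients aged 75 and over, but nothing in the protocol asks for bleeding to be recorded or compared between periods

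*Protocol*

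**What the plan says.** Section 6.4 describes the intervention as a checklist: "The care bundle comprises a list of items to follow and tick on a handover checklist". Three of its items are antithrombotic:

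- "Administration of dual antiplatelet therapy and transfer to cardiac intensive care unit if at least 2 of the followings" (the signs concern chest pain, ECG and troponin);
- "In case of atrial fibrillation: administration of heparin";
- "Preventive LMWH if no pre-existing anticoagulation therapy".

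For the control period the same section says "Treatments are given at the discretion of the treating emergency physician". Eligibility starts at age 75 (section 7.1).

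Section 10 says that "adverse events (serious and non-serious) do not need to be reported to the sponsor", and adds: "The report must instead be made as part of the vigilance procedure applicable to the product or intervention under investigation". The summary gives the reason for the light regime: "Minimal risk, as only recommended treatments will be administered".

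The secondary endpoints in section 4.2 are all-cause and cardiovascular death at 30 days, readmission, length of stay, and a more than twofold change in creatinine.

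**The concern.** Bleeding is the foreseeable harm of antithrombotic treatment, and the checklist is meant to make treatment more systematic. Section 2.1 reports that, of 73 patients in the preliminary survey, 23 had no work-up for precipitating factors, and that 17 of the other 50 had a factor found but not treated. Those factors include infection, so not all of that gap is antithrombotic, but acute coronary syndrome and atrial fibrillation are the other two.

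Section 2.6 expects a positive result to increase adherence to the bundle. A reader of such a result would want to know what happened to bleeding. The protocol treats one organ-specific harm, kidney function, as worth comparing, and has no counterpart for bleeding. A later analysis plan could not fill the gap, because it cannot analyse data that were never collected.

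**Working it through.** **1. Is bleeding asked for anywhere?** The places where it could stand:

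| Section | Content | Bleeding? |
|---|---|---|
| 4.2 Secondary endpoints | death, readmission, length of stay, creatinine | no |
| 6.1 Baseline and ED data | history, vital signs, laboratory values, treatments in the first 4 hours | no; haemoglobin only at baseline and only if measured |
| 6.3 Chronology table | day 30: in hospital, home or dead | no |
| 9.1, 9.2 Efficacy data | vital status, dates, creatinine, cause of death (cardiovascular or not) | no |
| 10 Safety | no reporting to the sponsor; product vigilance instead | no rate by period |
| 13.2, 13.3 Analyses | the endpoints above | no |

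Vigilance reports are no substitute: nothing links them to trial period or to a denominator.

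**2. Is the exposure recorded?** Yes. Section 6.1 lists antiplatelet, anticoagulant and LMWH use in the first 4 hours. The difference in use between periods can be reported; the difference in bleeding cannot.

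**3. What do the existing outcomes capture?** Section 9.1 scores a death as 0 days and subtracts hospital days, including readmissions.

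- Bleed that kills, prolongs the stay or causes readmission: counted in the primary endpoint and in the all-cause outcomes, but not identifiable as a bleed.
- Any other bleed: no trace.

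**4. The plan's own sample size (section 13.4).** Inputs: SD 9, difference 3 days, 80% power, 5% taken as two-sided.

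- Unadjusted total: 2 × 2 × [9 × (1.960 + 0.842) / 3]² = 282.6, stated as 283.
- With the design effect: 282.6 × 1.609 = 454.6, stated as 454.
- With 10% added: 454 × 1.10 = 499.4, stated as 500.

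These figures reproduce. None bears on bleeding.

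**5. What could a bleeding comparison show?** In the timetable of section 5.1, centre *i* spends *i* + 1 two-week blocks in control. The sum over 15 centres is 120 + 15 = 135 of 15 × 18 = 270 blocks, which is half. With even recruitment this gives 454 / 2 = 227 analysed patients per period. Carrying over the design effect as an assumption, 227 / 1.609 = 141 effective patients per period.

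The protocol gives no bleeding rate, so control rates *p* of 1%, 2% and 5% are assumed. The approximate 95% half-width at equal rates is 1.96 × √[2*p*(1 − *p*) / *n*]. The detectable rate is for 80% power, two-sided 5%, normal approximation with pooled variance under the null.

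| Assumed control rate | Half-width, n = 141 | Detectable rate, n = 141 | Half-width, n = 227 | Detectable rate, n = 227 |
|---|---|---|---|---|
| 1% | 2.3 points | 7.8% | 1.8 points | 5.7% |
| 2% | 3.3 points | 9.9% | 2.6 points | 7.6% |
| 5% | 5.1 points | 15.0% | 4.0 points | 12.4% |

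At 2%, about 227 × 0.02 = 4.5 events are expected per period. With so few, the normal approximation serves only to show the order of magnitude, and an exact or other small-sample interval is needed for the report.

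**The case against.** The strongest case against has four parts.

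- **Section 10 is about reporting, not recording.** It waives notification to the sponsor and is not wrong in itself. The eCRF is not shown, and section 12.2 leaves remaining variables to chart review. This stands as far as it goes: the sound statement is that no section asks for bleeding, not that its collection is excluded.
- **The primary endpoint already nets out serious harm.** This stands in large part. A reader might infer that a benefit could not be weighed against bleeding at all. The documents do not support that, because fatal bleeds, longer stays and readmissions all count against the intervention. What is lost is attribution, plus the bleeds that change none of these.
- **The extra exposure may be modest.** Two of the three items are conditional, control physicians may give all three, and section 6.4 has the guidelines recalled to physicians when the control period starts. A reader might infer that the bundle adds these drugs to every patient's care. The documents support only a possible difference in rates of use, of unstated size.
- **A bleeding comparison would be weak.** The trial is open, monitoring is at the minimal level (section 14.1), contact after discharge is by telephone, and no follow-up haemoglobin is scheduled. This also stands. It argues for a simple definition and an interval, not for leaving the outcome out.

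**Conclusion.** The gap is real and lies in data collection: the protocol records antithrombotic exposure in the ED but asks for no bleeding outcome, so bleeding cannot be estimated by period. It does not bias the primary comparison or make any stated figure wrong, and it implies nothing about which antithrombotic treatment is right. Adding the outcome is a cheap improvement that should be made.

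What it would buy is limited. Under an assumed 2% control rate and 141 effective patients per period, the interval would be about ±3 points (about 2 to 5 over assumed rates of 1% to 5%), and only a rise to about 10% would be detected with 80% power. That is enough to make a large excess visible or unlikely, and not enough to exclude a moderate one. These figures rest on the assumed rate, on even recruitment, and on the primary endpoint's design effect carrying over to bleeding.

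**What to change.** Add 30-day bleeding to section 4.2 as a secondary safety outcome.

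- **Definition:** fixed before the start and applicable from existing records, for example a bleed documented in the chart, or one leading to transfusion, readmission or death.
- **Collection:** the same in both periods, through the chart review and day-30 contact already planned in sections 6.1, 9.2 and 12.2. Charts are already source documents (section 12.3).
- **Reporting:** counts by period and the difference with an exact or other small-sample 95% interval, next to antithrombotic use by period; a descriptive estimate, not a test.

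The exemption in section 10 can stay as it is.

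Cost: a few eCRF fields and one table. Downsides to state openly: ascertainment by staff who know the period, no scheduled follow-up haemoglobin, telephone recall after discharge, and low precision.
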